#### Mechanism of Action

For research question 3 and hypothesis 3, we will elucidate the mechanism of change that links digital peer support intervention to emerging adult mental well-being (Figure 3). Specifically, we will assess whether and how the level at the start of the study and the rates of change from baseline to weeks 3, 6, and 9 in befrienders’ support relate to seekers’ mental well-being.

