**Aims and hypotheses**
Aim 1: the first aim is to evaluate the implementation effectiveness of digital peer support training between emerging adults providing support (befrienders) and emerging adults seeking help (seekers).Research question 1a: is Acceset digital peer support training an effective training curriculum in providing peer support?Hypothesis 1a: the digital peer support training is effective for befrienders in providing peer support, as demonstrated by the adoption of and fidelity to the training curriculum.Research question 1b: is the Acceset text-based intervention (ie, the platform) feasible and acceptable (ie, safe and timely) as an ongoing mechanism of support for seekers and befrienders?Hypothesis 1b: digital peer support is feasible and acceptable in offering support for emerging adults’ mental well-being, which is evidenced by 2 indicators:The engagement of the seeker-befriender-moderator interaction across the 4 time points—baseline (before the intervention), 3 weeks (conclusion of the intervention), and 6 and 9 weeks (carryover effect assessment)—that is indexed by the waiting period for seekers to receive a response. Delays are defined as a >48-hour waiting period and will be categorized based on the following reasons: (1) technical factors (eg, the befriender is not able to log into the platform to respond in time) and (2) human factors (eg, the befriender drops out from the study, and no replacement is found in time). An acceptable response time is within 48 hours, and this is emphasized during Acceset digital peer support training for befrienders [37].The use of technical features of the Acceset platform that is measured by the seeker dropout rate at each stage of engagement with the Acceset platform, the number of visits on the study registration website, the number of participants who registered with Acceset, the average number of letters exchanged, and the average number of emotion and functional adjustment stickers and motivation graphic interface formats used [37].Research question 1c: is the Acceset text-based intervention (ie, the platform) feasible and acceptable (ie, safe and timely) as an ongoing mechanism of support that identifies individuals who are at an unacceptably high risk of mental health conditions?Hypothesis 1c: digital peer support is feasible and acceptable in offering support for emerging adults’ mental well-being by identifying individuals who are at an unacceptably high risk of mental health conditions related to depression and suicidality, which is measured before and during engagement based on 3 means—specifically, the Acceset algorithm detection of the content of the letters, the moderators’ vetting of the content of seekers’ letters, and the seekers’ self-report responses to the 9-item Patient Health Questionnaire [38] (refer to the Implementation Outcomes section for details [37]).Aim 2: the second aim is to elucidate whether Acceset digital peer support harnesses the 4 components of emerging adult mental health—mattering, selfhood, compassion, and mindfulness.Research question 2a: does Acceset digital peer support enhance the 4 components among seekers and befrienders?Hypothesis 2a: Acceset digital peer support (training) increases the 4 components among befrienders (before and after training) and seekers (over the course of the study across 4 time points).Research question 2b: is Acceset digital peer support effective in improving emerging adult mental well-being?Hypothesis 2b: digital peer support leads to significantly better mental well-being of seekers compared with the control group. This effect is sustained beyond the period of the intervention.Aim 3: the third aim is to investigate the mechanism of change in emerging adult mental well-being involving digital peer support (delivered by the Acceset platform).Research question 3: what is the mechanism explaining the change in emerging adult mental well-being involving digital peer support?Hypothesis 3: the initial level and rate of change (ie, growth factors) of befrienders’ web-based support positively predict the growth factors of seekers’ psychological well-being in accordance with latent growth curve modeling.

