Befriender engagement will be monitored, and they will receive a reminder email after 48 hours if there is no reply to the seeker. A questionnaire battery over 4 time points will be used to monitor befrienders and seekers (Multimedia Appendix 3). These time points will include baseline (before the intervention), 3 weeks (end of the intervention), and 6 and 9 weeks (carryover effect measurement; Figure 1) [37]. Signals for closure will be done through an email reminder sent 7 days before the conversation ends, and another email will be sent to inform seekers and befrienders when the thread officially closes after 21 days. Where there are issues that reflect high negativity and suicidal thoughts and expressions at any point in the letter thread, we will immediately link the seekers to the appropriate professional counseling resource.

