The seeker-befriender interaction dynamic is facilitated digitally, with no in-person visits or interactions. Before and during the letter-writing process, a pop-up message reminds both befrienders and seekers that the use of the Acceset platform is to remain completely anonymous and that personal information may not be revealed in any way. In matching befrienders and seekers, 3 factors are considered: the timing when seekers reach out, the availability of befrienders, and befrienders’ knowledge of the nature of the seekers’ emotional experiences. Some befrienders may have more in-depth knowledge of certain issues based on their lived experiences and will prefer to support seekers on those issues. Thus, when the seekers write a letter, the social context of the letter is made known to the befriender, who will then select their preferred seeker based on their ability to relate and respond. The approach of matching befrienders and seekers is intended to facilitate effective peer support intervention [29]. Through the digital peer support training and the guidance of the moderators—certified counselors who will vet the e-letter drafts from the befrienders—the befriender’s role is to provide support by enhancing a sense of mattering, strengthening selfhood, exploring compassion, and cultivating mindfulness among seekers. Importantly, it is not the responsibility of the befriender to serve as an advisor, solve the seekers’ problems, or provide diagnoses of potential mental health issues.

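### Befrienders' web-based support (H3) and reply waiting time (H1b) are scheduled at baseline and weeks 3, 6 and 9, but letters exist only during the 21-day exchange

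*Protocol article*

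**What the plan says.** **The H3 predictor.** Hypothesis 3 (Textbox 1, Aims and hypotheses) takes as predictor "the initial level and rate of change (ie, growth factors) of" befrienders' web-based support, and Principal Findings repeats this. The section Mechanism of Action sets the occasions: "the level at the start of the study and the rates of change from baseline to weeks 3, 6, and 9 in" befrienders' support. Data Collection, Management, and Analyses assigns the question to latent growth curve modelling and says that linear, quadratic and nonlinear shapes will be compared.

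**The H1b indicator.** The first indicator for hypothesis 1b is "The engagement of the seeker-befriender-moderator interaction across the 4 time points", and the text then lists all four. It is an indicator "that is indexed by the waiting period for seekers to receive a response".

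**The schedule.** Participants and Study Setting says: "These time points will include baseline (before the intervention), 3 weeks (end of the intervention), and 6 and 9 weeks", the last two being for carryover. The same section gives arm 1 three weeks on the platform and says that "another email will be sent to inform seekers and befrienders when the thread officially closes after 21 days".

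**Pairing and contact.** Under Peer Emotional Disclosure, a befriender is matched once a seeker has written. The letter's social context is shown to the befriender, "who will then select their preferred seeker based on their ability to relate and respond". Participants and Study Setting rules out direct contact between the parties, and Peer Emotional Disclosure rules out meeting in person.

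**The concern.** Two sets of statements do not fit together. One treats befriender support and reply time as quantities that can be followed over nine weeks from a starting level. The other confines the only channel through which support is given, and through which a reply can be awaited, to the first three weeks after baseline.

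At baseline no letter has been written and no pair exists. At weeks 6 and 9 the threads are closed. Support delivered through the platform therefore has no initial level at the study's start and no value at the last two occasions.

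Aim 3 is at stake, because H3 rests wholly on this growth model and Principal Findings presents the mechanism of change as one of the novel contributions. If the analyst follows the stated schedule with delivered support, the model either cannot be estimated or returns growth factors produced by the opening and closing of the platform. The H1b wording has the same timing fault, with smaller consequences.

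**Working it through.** No figure in the protocol bears on this point, so there is none to reproduce. The check compares dates and then counts what a growth curve needs.

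**Step 1: occasions against the letter window.** Inputs are the four occasions (Participants and Study Setting; Mechanism of Action) and closure at day 21. Baseline is taken as day 0, before the first letter, because the protocol places it before the intervention.

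| Occasion | Day | Letters being exchanged? |
|---|---|---|
| Baseline | 0 | No, not started |
| Week 3 | 21 | Yes, last day |
| Week 6 | 42 | No, closed |
| Week 9 | 63 | No, closed |

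One of four occasions is usable. The window covers 21/63 = 33% of follow-up.

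**Step 2: what a growth curve needs.** With T occasions and g growth factors (2 for linear, 3 for quadratic):

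- observed moments = T + T(T+1)/2
- parameters = g + g(g+1)/2 + T, with a free residual variance at each occasion
- degrees of freedom (df) = moments − parameters

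| T | Shape | Moments | Parameters | df |
|---|---|---|---|---|
| 1 | linear | 1+1 = 2 | 2+3+1 = 6 | −4 |
| 2 | linear | 2+3 = 5 | 2+3+2 = 7 | −2 |
| 3 | linear | 3+6 = 9 | 2+3+3 = 8 | +1 |
| 3 | quadratic | 3+6 = 9 | 3+6+3 = 12 | −3 |
| 4 | linear | 4+10 = 14 | 2+3+4 = 9 | +5 |
| 4 | quadratic | 4+10 = 14 | 3+6+4 = 13 | +1 |

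With the single usable occasion the linear model is not identified. A linear shape needs at least three occasions inside the window. A quadratic shape needs at least four.

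**Step 3: what happens if zeros are entered.** Let a befriender's score at week 3 be s, with zeros at weeks 0, 6 and 9. For a least-squares line on weeks 0, 3, 6 and 9:

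- the mean week is 4.5 and the deviations are −4.5, −1.5, 1.5 and 4.5, with sum of squares 20.25 + 2.25 + 2.25 + 20.25 = 45
- slope = (−1.5 × s)/45 = −s/30 per week
- intercept = s/4 + 4.5 × s/30 = 0.25s + 0.15s = 0.40s

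Every befriender with s > 0 shows a decline, fixed by when the platform closes. Initial level and slope are both fixed multiples of the same number, so they cannot act as two separate predictors. Three of the four measures also have no variance.

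**Step 4: waiting time.** A waiting time starts when a letter is sent in an open thread. Step 1 therefore applies unchanged: none exists at baseline, week 6 or week 9.

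**The case against.** The strongest reply is that the predictor need not come from letters. Participants and Study Setting gives befrienders a questionnaire battery at all four time points, and the section on implementation and clinical study outcomes says that all outcomes are measured with it. The battery (Multimedia Appendix 3) and the model diagram (Figure 3) are not shown. A condensed article may also leave the exact variable to a fuller document. A reader might infer that the growth model has no valid predictor at all. The documents do not support that, because a four-occasion self-report score may exist.

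This limits the point but does not remove it. The only support scale named under Clinical Outcomes is the Multidimensional Scale of Perceived Social Support, which measures support received. H3 names web-based support. A befriender's score taken before any match, or after the thread has closed, would describe something else.

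On H1b, Implementation Outcomes defines the wait per response with a 48-hour limit and ties it to no occasion. Waiting time is also nowhere said to enter the growth model. A reader might infer that the H1b fault undermines that model, or that waits would be reported for periods without letters. Neither follows. H1b is a parallel error of wording.

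Parameter counts for a full two-process model against 50 seekers would depend on a specification that the protocol does not give, so they are not relied on here. Befrienders' choice of seeker does not make the predictor invalid either. It limits how the result may be interpreted.

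**Conclusion.** The contradiction is in the stated text. On the protocol's own schedule, delivered support and reply waiting time can be observed at one of four occasions. A growth curve of delivered support is then unidentified (df −4 for a linear shape), or, with zeros filled in, an artefact of the opening and closing dates.

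This rests on two assumptions: baseline precedes the first letter, and no support passes outside the platform. Both follow from the text. When the wait-listed arm gains access is not stated, so letters in that arm cannot be assessed and H3 is read as an arm 1 analysis.

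The fault affects Aim 3 and the wording of H1b. The randomised comparison of seekers under H2b is untouched. Even with a sound exposure measure, H3 can show only an association, because the amount of support is not randomised and befrienders choose whom they support.

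**What to change.** Reconcile Textbox 1, Mechanism of Action, the growth-model text and Principal Findings with the schedule in Participants and Study Setting:

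1. **Define the H3 support measure** from time-stamped letters within days 0-21, naming the variable (for example letter count, reply latency or coded component score). Use at least three occasions for a linear shape, such as weeks 1, 2 and 3, and at least four if a quadratic shape is kept with free residual variances.
2. **Relate it to seekers' well-being** at weeks 3, 6 and 9, adjusting for baseline well-being and allowing for seekers clustered within befrienders.
3. **Report H3 as a non-randomised association within arm 1.**
4. **If a questionnaire score is meant instead**, name the scale and its occasions, and do not call it web-based support at times when no thread is open.
5. **Restrict H1b waiting time** to letters in open threads, days 0-21.

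The cost is rewording. Data Collection, Management, and Analyses already has letter content stored against participant IDs, and send and reply times are needed anyway for the 48-hour criterion. The downside is a less ambitious H3. Results reports that analysis began in July 2022, so the change should be dated. A mediation analysis using both arms would answer a different question. It would be a separate, exploratory, post hoc addition and is not part of this fix.

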**Figure 3 figure3:**
[figure not shown]
A mechanism of change linking befrienders’ web-based support and seekers’ psychological well-being.

### Data Collection, Management, and Analyses

Acceset will serve as the data collection platform. Participants (both seekers and befrienders) will initially enter their details on the sign-up page, which includes role preference (seeker, befriender, or either), email, date of birth, gender, nationality, ethnicity, monthly household income, and password. The user will be required to answer the PHQ-9 to determine their eligibility. An email will also be sent to the users’ registered email address for verification. Once eligible individuals are selected and assigned their respective roles, they will be given a unique nonidentifying ID to participate in the study. Participants’ self-reported questionnaire responses at each time point and the digital letter exchange content will be securely stored and tied to their specific IDs. The data collected will be stored on the cloud servers of the leading author’s affiliated institution. Once the research concludes, the information will be downloaded to a Microsoft Excel sheet, and all personal information will be deidentified for data analyses.

A power analysis assessed the adequate sample size needed for the RCT to have sufficient power to detect valid effects. The intervention (n=50) and control (n=50) arms were derived from multiple dependent variables assessing implementation testing (ie, feasibility and utility) and clinical outcomes. To address any potential challenges with missing data, the Little Missing Completely at Random Test will address potential missing data via full information maximum likelihood imputation [37,59]. Maximum likelihood estimation is a method that ascertains the parameter values of a model using the mean and variance and maximizes the chance that the values generated are closest to those observed.

The following approaches will be used for data analysis and interpretation. Independent-sample 2-tailed *t* tests will compare the intervention and control groups. Bonferroni post hoc tests will control for multiple comparisons. For both the intervention and control groups, additional independent *t* tests will compare seekers who provided data across all 4 time points with those who dropped out from the study for different reasons to ascertain if the sample with data across all 4 time points and the sample with fewer data points bias our results. For instance, seekers may drop out when risk assessments identify them as having a high risk of depression and suicidality during the course of the study. There will also be instances when befrienders discontinue the letter writing because of the sensitive nature of the letter content that may cause distress and befrienders not being fully comfortable, and the system will inform the seekers and obtain their consent to end the letter thread instead of continuing the conversation with a new befriender. Second, each participant’s emotional experiences disclosed on Acceset will be extracted based on the definitions of the 4 components of psychological well-being. Latent Dirichlet allocation analyses in R (R Foundation for Statistical Computing) and content analysis will be used [37,60,61].

Latent growth curve modeling (LCM) will investigate the mechanism of change involving the trajectories of peer support in predicting the change in psychological well-being [59]. LCM delineates whether and how the exposure to the intervention changes over time with psychological outcomes by estimating and comparing different baseline latent growth models, including linear, quadratic, and nonlinear curve fitting (ie, optimal fit). In other words, LCM elucidates whether the trend in befrienders’ peer support predicts the trend in seekers’ psychological well-being (Figure 3). Current research assessing peer support intervention for the mental health of young people does not consider the mechanism of change. By establishing a change model, this protocol provides a basis for building the therapeutic potential of digital peer support that harnesses the components of emerging adult mental well-being to reduce psychological symptoms. Specifically, LCM elucidates whether and how the intervention affects the development of psychological symptoms and how they unfold over time among emerging adults. This finding provides actionable knowledge for timely and relevant digital peer support.

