### Participants and Study Setting

We plan to recruit 130 participants (100 seekers and 30 befrienders) at the National University of Singapore (NUS) to engage with the Acceset intervention in accordance with an Institutional Review Board–approved protocol. Participants will be recruited via the Research Participation program within the Department of Psychology at NUS, where students will be awarded credits as part of the introductory courses for psychology. During recruitment, inclusion and exclusion criteria screening will be conducted via self-reporting. Participants qualified for inclusion (seekers) will be randomized into 2 arms. The seekers (n=50), befrienders (n=30), and moderators (n=30) in arm 1 will use Acceset for 3 weeks. The control group (n=50) in arm 2 will be wait-listed for Acceset use. It should be noted that the wait-listing approach is a standardized approach for RCTs pertaining to digital mental health [37,39,40].

We will recruit age- and gender-matched individuals from NUS. The 4–time-point questionnaire battery of arm 1 will be used to compare the mental well-being and help-seeking behavior with those in arm 2 [37]. Moderators will be recruited from the Singapore Executive Counselling and Training Academy. If an unacceptably high risk of depression and suicidality is detected at any time point by the moderator, who is a certified counselor, they will reach out to the participant, who will be directed to different clinical mental health support providers, including counseling centers and hotlines, on the NUS campus. On the basis of power analysis and the finding that 20% to 40% of the emerging adults enrolled in an IHL typically experience distress, this sample will provide a sufficiently powered comparator group.

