#### Clinical Outcomes

To address research question 2a and hypothesis 2a, we will examine whether the Acceset training curriculum can enhance the 4 components of psychological well-being among befrienders and seekers. We will compare the change in mattering, selfhood, compassion, and mindfulness scores of befrienders between baseline and following Acceset training (ie, before vs after training) and those of seekers over the course of the study. As for research question 2b and hypothesis 2b, we hypothesized that engagement with Acceset digital peer support will lead to improved mental well-being of the seekers compared with the control group and that this effect may be sustained beyond the period of the intervention. To assess these effects, we will evaluate the change in mental well-being of the participants in both study groups (intervention and control) after 3, 6, and 9 weeks from baseline using self-report questionnaires. Seekers will provide responses pertaining to help-seeking behavior beyond the Acceset platform at weeks 6 and 9 using the perceived social support measure in the questionnaire battery. We will assess the correlations of the 3 digital features—comprising emotion and functional adjustment stickers and motivation GIFs, which reflect seekers’ mental well-being during engagement with the platform—with their well-being scores from the questionnaires.

The scale or set of scales used to assess the clinical outcomes, including the 4 components of psychological well-being underpinning the Acceset training curriculum, measures of seekers’ well-being, and perceived social support, are outlined in the following paragraph.

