## Results

This protocol received approval from the Institutional Ethics Review Board of NUS in October 2021. Recruitment will commence in January 2022. Data collection began in March 2022 and was completed in June 2022. Data analysis started in July 2022 and is currently in progress. We aim to report the preliminary study outcomes in December 2022. The effect size will be analyzed using the Cohen *d* index with a significance level of .05 (95% reliability) and 80% power statistic [37]. A total of 100 seekers, 35 befrienders, and 2 moderators were recruited in January 2022.

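### The arm comparison is fixed as independent t tests, without baseline adjustment or a joint model of weeks 3, 6 and 9, and is not linked to the stated maximum likelihood handling of missing data

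*Protocol article*

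**What the plan says.** On timing, Participants and Study Setting has the questionnaire battery given four times: "These time points will include baseline (before the intervention), 3 weeks (end of the intervention), and 6 and 9 weeks". Clinical Outcomes says that the change in well-being will be evaluated in both arms "after 3, 6, and 9 weeks from baseline using self-report questionnaires".

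On the arm comparison, Data Collection, Management, and Analyses says: "Independent-sample 2-tailed *t* tests will compare the intervention and control groups". Bonferroni is to handle multiple comparisons, but the number of comparisons is not given. The same section adds t tests of seekers with complete data against those who dropped out, and gives identification as high risk during the study as one example of why a seeker may drop out.

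On missing data, that section says "the Little Missing Completely at Random Test will address potential missing data via full information maximum likelihood imputation". It does not say which analysis this feeds.

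The only longitudinal model named is a latent growth curve model, presented as the analysis of how befrienders' support relates to seekers' well-being (aim 3).

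On size, "The intervention (n=50) and control (n=50) arms were derived from multiple dependent variables", and Results reports that the effect size will be analysed "with a significance level of .05 (95% reliability) and 80% power statistic".

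**The concern.** Hypothesis 2b claims a better outcome than control that lasts beyond the three-week intervention. The data to test this efficiently are collected: a baseline and three follow-ups in both arms. The stated test takes one visit at a time and has no term for baseline, so a lasting benefit would be read from separate tests at weeks 6 and 9.

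Two things are at stake. The first is precision, in a trial of only 50 per arm. The second is the handling of dropout. The article intends a likelihood method for missing data, but an ordinary t test has no such step and leaves out whoever is missing at the visit. If the seekers who leave are those with worse recorded scores, the remaining arms are no longer the randomised arms. Comparing completers with dropouts may reveal that bias but does not remove it.

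**Working it through.** **The stated sample size.** The article says "A power analysis assessed the adequate sample size needed for the RCT to have sufficient power to detect valid effects" but gives no effect size or SD, so 50 per arm cannot be reproduced. It can only be solved backwards. Detectable d = (1.960 + 0.842) × √(2/50) = 2.802 × 0.2 = 0.56, or 0.57 by the exact t calculation. An effect of d = 0.5 would need 63 to 64 per arm.

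**Inputs.** From the article: 50 per arm, two-sided alpha .05, 80% power. Assumed, because the article is silent: d = 0.5, equal SD of 1 at baseline and follow-up, r from 0.3 to 0.7, and no Bonferroni division.

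**Variance factors, relative to a post-score t test (1).**
- Change-score t test: 2 − 2r
- Baseline-adjusted comparison (ANCOVA): 1 − r²

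**Power** = Φ(0.5 / (0.2 × √factor) − 1.96). For example, ANCOVA at r = 0.5: 0.5 / (0.2 × 0.866) − 1.96 = 0.93, which gives 82.3%.

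| r | Post-score: power | Change score: factor, power | Baseline-adjusted: factor, power |
|---|---|---|---|
| 0.3 | 70.5% | 1.40, 56.1% | 0.91, 74.6% |
| 0.5 | 70.5% | 1.00, 70.5% | 0.75, 82.3% |
| 0.7 | 70.5% | 0.60, 89.8% | 0.51, 93.8% |

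Detectable d at 80% power is 0.56 for the post score. For r = 0.3, 0.5 and 0.7 it is 0.66, 0.56 and 0.43 for change scores, and 0.54, 0.49 and 0.40 with adjustment.

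**Adjustment against change scores.** The variance ratio is (1 − r²)/(2 − 2r) = (1 + r)/2, which is 0.75 at r = 0.5 and 0.85 at r = 0.7. That is worth 100/0.75 = 133 and 100/0.85 = 118 seekers in place of 100. Below r = 0.5 the change-score factor exceeds 1, so change scores do worse than the post score alone.

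**Bonferroni.** Dividing alpha by three (an assumption: one test per follow-up visit) raises the post-score detectable d to 0.65. Any such division lowers every power in the table but does not change the ranking at a given r.

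**Missing visits.** The article gives no dropout rate. For a post-score t test on seekers seen at the visit, losing 10%, 20% or 30% (assumed) cuts power at d = 0.5 from 70.5% to 66.0%, 60.9% or 55.2%.

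**Dropout linked to scores.** A simulation of 3,000 trials assumed equal correlation r between all visits, a true difference of −0.50 and dropout more likely after a high score at week 3 or 6. About 18% were missing at week 9.

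| r | Post-score t test on those seen: mean (SE) | Baseline-adjusted on those seen | Likelihood-type, baseline and earlier visits |
|---|---|---|---|
| 0.5 | −0.45 (0.215) | −0.47 (0.189) | −0.50 (0.190) |
| 0.7 | −0.43 (0.208) | −0.48 (0.160) | −0.50 (0.158) |

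Baseline supplies most of the gain in precision; using the earlier visits as well removes the remaining bias. A change-score t test was not simulated.

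**The case against.** The best defence is that a t test between randomised arms is valid, that this is a condensed article, and that covariates and covariance structures normally belong in an analysis plan that is not shown. That stands for model detail. It does not cover the choice of test, which the article itself fixes.

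Several stronger readings are tempting but unsupported:

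- **That baseline is ignored.** Clinical Outcomes speaks of change from baseline, so change-score t tests are the more natural reading. Equating baseline adjustment with up to 196 seekers (100/0.51), or with a rise in power from about 70% to 94%, holds only against a post-score test at r = 0.7. Against change scores at that r the rise is 4 points.
- **That full information maximum likelihood cannot be used.** A two-group mean comparison can be fitted that way, or a t test run on likelihood-imputed data. What is missing is the link.
- **That incomplete seekers are dropped.** No such rule is stated. It is how an ordinary t test behaves, and the article does plan a check of completers against dropouts.
- **That repeated visits go unanalysed.** One sentence says the growth model will show whether and how the intervention affects symptoms over time. But no arm term is described, and its predictor is befriender support, which wait-listed seekers do not receive during the three weeks. Hypothesis 2b therefore still rests on the t tests.

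Age and gender are a minor matter: "We will recruit age- and gender-matched individuals from NUS" does not make clear what is matched to what.

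**Conclusion.** The point holds as a matter of efficiency and internal fit. The arm comparison is set as t tests with no baseline covariate and no joint model of follow-up, and it is not connected to the missing-data method in the same section. With d = 0.5, 50 per arm, unadjusted alpha and r of 0.5 to 0.7, baseline adjustment gains about 12 to 4 percentage points of power over change scores (82.3 − 70.5; 93.8 − 89.8) and about 12 to 23 over post scores (82.3 − 70.5; 93.8 − 70.5). At r = 0.3 it gains about 4 points over post scores and 18 over change scores. The gain is likely to be smaller for PHQ-9, because eligibility caps its baseline at 9.

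The correlation, effect size and dropout figures are assumptions, so these numbers show direction and likely size, not the trial's actual power. Nothing here shows the sample size to be wrong or the trial to be invalid. This should be corrected, but it is not fatal.

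**What to change.** For each outcome, make the arm comparison a likelihood-based mixed model of all visits with arm, week, arm-by-week and the baseline value. Baseline can be a covariate. Alternatively, it can be a response with means constrained equal across arms, which also keeps seekers who have a baseline only. Report the arm difference at week 3 for the immediate effect, and at weeks 6 and 9 for the claim of a lasting one. Age and gender are optional covariates.

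State that this model is where the maximum likelihood handling of missing data applies. It relies on dropout being explained by the values in the model. For outcomes other than depression, therefore, consider adding PHQ-9 as an auxiliary variable or in a sensitivity analysis. Keep the completer-versus-dropout tests as description.

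No new data are needed; the cost is revised analysis text and code. However, Results says that data collection ended in June 2022 and analysis began in July 2022, so this would be a change made after the data were in hand. Date it, disclose it, say whether arm comparisons had already been seen, and report the published t tests alongside the model.
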